### Analysis

#### Key components of FBT (question 1)

The Key Measures of Therapist Behaviours and Self-Efficacy in FBT will be examined to determine the percentage of therapists reporting that they completed all key components of FBT (weighing their patient, using externalization, using agnosticism, and doing a family meal in session 2 within vFBT).

#### Fidelity to the vFBT model (question 2)

The percentage of therapists demonstrating vFBT fidelity will be determined by the FBT fidelity rating scale (FBT-FACT [39]) rated by experts and achieving a 4/7 average score or greater on each session [40].

#### Implementation team and patient/family experiences of vFBT (question 3)

Transcripts from the end of study focus groups with teams and patients/families will be analyzed using conventional content analysis and the constant comparison technique [47]. Specifically, iterative reviews of text within and across transcripts will be completed by two members of the research team to identify codes and associated categories characterizing implementation team and patient/family experience with vFBT, their suggestions for change (if any), and to provide a rich description of their perceptions of the value and impact of the vFBT model. Codes and categories will be grouped into overarching themes that help to synthesize the qualitative data and address our research questions. In terms of quantitative measures, changes over time in readiness for change, attitudes toward evidence-based practice, and confidence related to vFBT will be analyzed using repeated measures ANOVA (using SPSS software). We will also examine demographic characteristics of therapists, medical practitioners, and program administrators including age, gender, academic discipline/area of expertise, and number of years in their current role, in relation to implementation success.

#### Patient outcomes (question 4)

As mentioned above, therapists will provide weekly data on patients’ weight and number of binge/purge episodes per week before starting vFBT and after each of the first four sessions of vFBT (using Qualtrics). Changes in weight and average number of binge/purge episodes per week over time will be analyzed using repeated measures ANOVA (using SPSS software). Weight gain will be compared against the benchmark of 2 kg gain after four sessions in standard FBT as a measure of clinical implementation success. Patient demographics, including age, gender, and number of years with the ED, will be examined in relation to outcome.

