#### Patients

To participate in this study, patients must be under 18 years of age; have a diagnosis of Anorexia Nervosa; live in Ontario, Canada; have the ability to read, understand, speak, and write in the English language; and have access to a working computer/electronic device with a stable Internet connection.

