### Sample size

The four ED programs participating in the study average two therapists per program, yielding an approximate sample size of eight therapists, four medical practitioners, and four program administrators. We are aiming to recruit one family with an eligible patient per therapist at each site (eight families total). Although a sample size calculation was not completed, we believe this is an appropriate sample size for a feasibility study with this population.

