#### Patient outcomes (question 4)

Patient outcomes including weight and number of binge/purge episodes per week will be recorded at treatment baseline (at the time of patient consent) and then submitted on a weekly basis after each of the first four vFBT sessions by the therapist (using Qualtrics). Weight gain of at least 2 kg following the first four sessions of FBT is highly predictive of final treatment outcome [45, 46] and is a valid measure of overall clinical effectiveness. This will be our benchmark for comparing vFBT effectiveness to standard FBT. Patient demographics and diagnosis will be collected at treatment baseline (at the time of patient consent).

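### Repeated measures ANOVA suits the binge/purge outcome poorly: patients with no episodes dilute the mean change, and with two or fewer symptomatic patients of eight the test cannot reach p < 0.05

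*Protocol article*

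**What the plan says.** Four places in the protocol article define this analysis.

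- **Population.** Under Eligibility criteria, Patients, a patient must "have a diagnosis of Anorexia Nervosa". No bingeing or purging is required.
- **Number of patients.** Sample size plans one family per therapist, "eight families total". It also states: "Although a sample size calculation was not completed".
- **Outcome and timing.** Under Measures, Patient outcomes (question 4): "Patient outcomes including weight and number of binge/purge episodes per week will be recorded at treatment baseline". Under Analysis, the same heading gives the schedule as "before starting vFBT and after each of the first four sessions of vFBT", which makes five time points.
- **Method.** Analysis, Patient outcomes (question 4): "Changes in weight and average number of binge/purge episodes per week over time will be analyzed using repeated measures ANOVA". Nothing there limits the binge/purge analysis to patients who have such episodes.

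Weight has a second stated analysis, the comparison with the 2 kg benchmark. For binge/purge frequency the ANOVA over time is the main stated analysis and there is no benchmark.

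**The concern.** A patient with anorexia nervosa who neither binges nor purges contributes zero at every time point. Such a patient cannot improve on this outcome, but still counts in the denominator of the mean and in the error degrees of freedom. This has two effects.

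First, the average change over all patients is pulled towards zero and describes neither group. It varies with the mix of patients enrolled, even if the response among symptomatic patients is the same.

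Second, if very few patients are symptomatic, the F statistic has a ceiling that does not depend on how far or how fast their counts fall. A non-significant result would then say how many patients had no episodes. It would say nothing about what happened under virtual treatment.

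Research question 4 asks whether outcomes resemble those of standard treatment, and the ANOVA would be poor evidence on that question for this outcome.

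**Working it through.** **Inputs.**
- n = 8, from Sample size: 4 programs × about 2 therapists × 1 family = 8. This reproduces the planned number. There is no power calculation to reproduce.
- k = 5 time points: baseline plus four sessions.
- Alpha is not stated; 0.05 is assumed.
- m, the number of patients with a non-zero count at any time point, is not stated. Values of 1 to 4 are shown.

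**Dilution.** Suppose two patients each go from 14 episodes per week to 0 and the other six have none. The mean fall among the symptomatic patients is 14. The whole-sample mean fall is (2 × 14)/8 = 3.5.

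**Ceiling on F.** Let c_i be patient i's five counts minus that patient's own mean. For patients at zero throughout, c_i = 0. Write T for the sum of |c_i|² over the m others.
- SS_time = |Σc_i|²/n, which by Cauchy-Schwarz is at most mT/n.
- SS_error = T − SS_time, which is at least T(n−m)/n.
- F = (n−1) × SS_time/SS_error, so F ≤ m(n−1)/(n−m).

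Equality needs identical centred profiles in the m patients. The size and timing of the fall cancel out. With m = 1, F is exactly 1 for any trajectory that changes.

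**Numbers for n = 8, k = 5.** The critical F(4,28) at 0.05 is 2.714. With identical profiles the Greenhouse-Geisser epsilon is 0.25, so the corrected reference is F(1,7).

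| m | Maximum F | p at that F, uncorrected | p at that F, Greenhouse-Geisser |
|---|---|---|---|
| 1 | 7/7 = 1.00 | 0.42 | 0.35 |
| 2 | 14/6 = 2.33 | 0.080 | 0.17 |
| 3 | 21/5 = 4.20 | 0.009 | 0.080 |
| 4 | 28/4 = 7.00 | 0.0005 | 0.033 |

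**Direct checks for m = 2.**
- Both patients following 14, 0, 0, 0, 0, or both following 14, 7, 3, 1, 0, gives F = 2.33 and p = 0.080.
- Complete cessation after baseline from unequal baselines of 14 and 3 gives F = 1.50 and p = 0.23.
- Among 200,000 random two-patient data sets, none gave p below 0.080 uncorrected or below 0.170 with Greenhouse-Geisser.
- With 4 to 7 patients analysed instead of 8, the smallest uncorrected p is 0.063 to 0.078. Only with 3 patients analysed does it fall below 0.05 (0.045).

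**How likely is m ≤ 2?** The article gives no proportion, so a range is assumed. With p the chance that a patient has any episodes during the five weeks recorded, P(m ≤ 2) = (1−p)⁸ + 8p(1−p)⁷ + 28p²(1−p)⁶.

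| Assumed p | P(m ≤ 2) |
|---|---|
| 20% | 0.797 |
| 30% | 0.552 |
| 40% | 0.315 |
| 50% | 0.145 |

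**The case against.** **The ceiling is conditional.** A reader might infer that the test must return no change whatever happens. The documents do not support that. They do not give m. With three symptomatic patients the uncorrected p can be as low as 0.009, and with four the ceiling does not prevent significance even after correction in the identical-profile case. At 40% or 50% symptomatic, m is more likely than not to exceed two. This objection stands, and the claim is limited accordingly.

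**A real response being reported as a null finding.** This is another tempting inference. The article states no alpha, no significance rule and no success criterion for binge/purge frequency, and it does not rule out descriptive reporting beside the ANOVA. How a non-significant result would be worded is unknown. This also stands.

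**Any test would fail with two changers.** A two-sided exact sign test on two patients has a smallest p of 2 × (1/2)² = 0.5. The lack of significance therefore reflects how little information there is, more than a defect peculiar to ANOVA. The study also calls itself a feasibility and pilot study. This is right, and it makes dilution the stronger criticism. It does not defend the planned test, because a small feasibility sample is a reason to describe this outcome.

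**The analysis set might be restricted elsewhere.** The ceiling would not apply to an ANOVA of symptomatic patients only. The article neither states nor suggests such a restriction, and its text reads most naturally as covering all patients.

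**Zero at baseline is not zero throughout.** A patient may develop episodes during treatment, which raises m and loosens the bound. That is why m is defined here as a non-zero count at any time point, and why onset needs its own report.

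**Conclusion.** The concern holds in conditional form. The stated analysis is ill-suited to this outcome because patients without episodes dilute the mean change and make the result depend on the mix enrolled. That part needs only that some patients without episodes are enrolled, which the eligibility criteria allow.

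The ceiling adds to this when few patients are symptomatic. At an assumed alpha of 0.05, with all eight analysed, one or two symptomatic patients cannot produce a significant time effect even if they stop completely. At m = 3 the same is true of identical profiles after Greenhouse-Geisser correction. Under the assumed 20% to 50% range, the chance of two or fewer runs from 80% down to 14%.

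It would go too far to say that the test fails by construction or that a true response will be reported as none: the documents fix neither m, nor alpha, nor a decision rule for this outcome. The point does not extend to weight. It should be changed, but it affects one outcome without a benchmark in a small feasibility study.

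**What to change.** Make the binge/purge analysis descriptive.

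- For patients with at least one episode per week at baseline, list the five weekly counts for each patient. Report the median change, the number with a reduction and the number with cessation.
- Report separately the number of patients with zero at baseline who develop episodes.
- State that a non-significant whole-sample ANOVA, if one is run, will not be interpreted as evidence of no change.

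This is a change of wording and needs no new data, since the weekly counts are already collected. Trial status says that no data cleaning or analysis had taken place, so on that account the change can still be made in advance. The cost is that this outcome has no significance test, which with so few patients would have told little.

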At the time of this writing, COVID-19 cases are increasing exponentially, and health care workers are experiencing fatigue, and some are falling ill. As such, hospital departments may become even more understaffed and overworked. With ED programs across Ontario seeing more than three times the typical number of referrals for outpatient care, and an unprecedented number of children requiring inpatient hospitalization, therapists, medical practitioners, and program administrators participating in our study may no longer have time to commit to implementation activities and the tension for change may shift to more pressing demands for the time being. As there is much uncertainty surrounding the recession of the COVID-19 pandemic, it is nearly impossible to fully anticipate the impact it will have on those conducting research, implementing new treatment modalities, and providing clinical care.

In summary, this is the first clinical trial to evaluate the implementation of vFBT in pediatric EDs, specifically with children and adolescents with Anorexia Nervosa. Challenges to date include obtaining ethics approval at participating sites and difficulties in recruiting additional sites to join our study. Results from this trial have the potential to provide valuable information about adaption from in-person to virtual care and how best to implement vFBT in pediatric ED treatment in Ontario, which will be useful when considering treatment for those in remote areas where in-person specialized care may be unavailable or inaccessible. In addition, this research will help to inform further studies on how the virtual delivery of FBT compares with in-person “gold standard” models. Future studies could explore the costs associated with the implementation and virtual delivery of vFBT in comparison to standard, in-person FBT.

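### Repeated measures ANOVA keeps only subjects with every record, which a study of about eight patients and eight therapists can ill afford; use all available records and report the session-4 gain with an interval

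*Protocol article*

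**What the plan says.** The Analysis section on patient outcomes (question 4) states: "Changes in weight and average number of binge/purge episodes per week over time will be analyzed using repeated measures ANOVA (using SPSS software". The Analysis section on experiences (question 3) names the same method for readiness, attitudes and confidence: "confidence related to vFBT will be analyzed using repeated measures ANOVA (using SPSS software".

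Patient data are due "before starting vFBT and after each of the first four sessions of vFBT (using Qualtrics", which makes five records per patient. The Measures section on patient outcomes says that they are "then submitted on a weekly basis after each of the first four vFBT sessions by the therapist (using Qualtrics". Therapists complete their own scales three times: at consent, after the training workshop, and after session 4.

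The Sample size section expects roughly eight therapists and, for patients: "We are aiming to recruit one family with an eligible patient per therapist at each site (eight families total". It adds: "Although a sample size calculation was not completed, we believe this is an appropriate sample size for a feasibility study with this population".

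Directly after naming the ANOVA for patients, the protocol says that weight gain will be set against a benchmark of 2 kg after four sessions. It does not say whether this is a mean, a test or a proportion, and it attaches no interval. Missing records are not mentioned in either analysis section.

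**The concern.** Classical repeated measures ANOVA needs a complete row for each subject. A patient with four of five weights, or a therapist with two of three questionnaires, contributes nothing. In a large trial that is a modest waste. With about eight subjects, each loss removes an eighth of the sample, and most of what is lost is data that were collected.

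Missed forms are plausible on the protocol's own account. The Discussion warns that therapists, medical practitioners and program administrators "participating in our study may no longer have time to commit to implementation activities", and therapists submit both the weekly patient forms and their own scales.

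Once a record is missing, the result describes completers. If missingness is related to how the patient or therapist is progressing, the result is biased.

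The F-test asks whether the time-point means differ at all. Question 4 asks whether outcomes resemble those of standard FBT, judged by gain at session 4 against 2 kg. A significant or non-significant F does not answer that.

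**Working it through.** **Inputs from the protocol.** Eight patients and about eight therapists (Sample size); k = 5 records per patient (Patient outcomes, question 4); k = 3 per therapist (Measures, question 3); benchmark 2 kg (Patient outcomes). No sample size calculation was done, so the plan has no figure of its own to reproduce.

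**Assumed.** A missing rate m per record of 2%, 5% or 10%, equal and independent across records. The protocol gives no rate.

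**Step 1: subjects left.** Expected complete subjects = 8 × (1 − m)^k. Chance of losing at least one patient = 1 − (1 − m)^(8 × 5).

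| m | Patients, k = 5 | Chance of losing at least one patient | Therapists, k = 3 |
|---|---|---|---|
| 2% | 8 × 0.98^5 = 7.2 | 55% | 8 × 0.98^3 = 7.5 |
| 5% | 8 × 0.95^5 = 6.2 | 87% | 8 × 0.95^3 = 6.9 |
| 10% | 8 × 0.90^5 = 4.7 | 98.5% | 8 × 0.90^3 = 5.8 |

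If the baseline record, taken at consent, is never missing, the patient exponent falls to 4 and the expected numbers are 7.4, 6.5 and 5.2.

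**Step 2: collected patient records discarded.** Records collected = 40 × (1 − m). Records used = 40 × (1 − m)^5.

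- 2%: 39.2 collected, 36.2 used, 3.0 discarded (8%)
- 5%: 38.0 collected, 31.0 used, 7.0 discarded (19%)
- 10%: 36.0 collected, 23.6 used, 12.4 discarded (34%)

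**Step 3: what the benchmark needs.** Gain at session 4 uses two records, so 8 × (1 − m)^2 patients are informative: 7.7, 7.2 and 6.5. At 10%, requiring all five records costs a further 6.5 − 4.7 = 1.8 patients.

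**Step 4: width of the missing interval.** The half-width of a 95% CI for mean gain is t(0.975, n − 1) × SD / √n. This is 2.365/√8 = 0.84 SD for n = 8 and 2.571/√6 = 1.05 SD for n = 6. The protocol gives no SD of change. For an assumed 1, 1.5 or 2 kg:

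- n = 8: ±0.84, ±1.25 or ±1.67 kg
- n = 6: ±1.05, ±1.57 or ±2.10 kg

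These widths are large beside a 2 kg benchmark, so the comparison says little without its interval.

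**Step 5: the multivariate form.** With five time points the multivariate test has 4 and n − 4 degrees of freedom: 4 and 4 with eight complete patients. It cannot be computed with four or fewer, a number close to the 4.7 expected at 10% missing.

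**The case against.** **The loss depends on assumed missingness.** This stands. If every record arrives, nothing is discarded. In a simulation with assumed inputs (mean gain 0.4 kg per week, SD of individual slopes 0.4, residual SD 0.4 kg), ANOVA with a Greenhouse-Geisser correction had 65% power on complete data, against 64% for per-patient slopes. Under listwise deletion the ANOVA fell to 58%, 48% and 34% at 2%, 5% and 10% missing. Slopes from all available weights kept about 62% at 10%. Follow-up is short, and weighing is a core part of the therapy, so low rates are possible.

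**This is a small feasibility study, and patient outcome is the last of four questions.** That limits the weight of power figures. It does not favour discarding data, since a feasibility study mainly needs usable estimates.

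**Details may sit in an unseen analysis plan.** That answers an omission, but here the article names the method.

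Four stronger readings are tempting and are not supported:

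- *That the plan has no session-4 comparison.* It has one, in the sentence after the ANOVA. What is missing is its form and its uncertainty.
- *That the protocol expects enrolled patients to be hospitalised.* The Discussion does mention "an unprecedented number of children requiring inpatient hospitalization", but across Ontario programs and as a source of staff workload. It predicts no patient dropout and links no missing form to poor weight gain.
- *That completers would falsely meet the benchmark.* One can build such a case. With an assumed true gain of 0.35 kg per week (4 × 0.35 = 1.4 kg) and every patient without gain by session 2 removed (23.5% of patients under the assumed inputs), completers average 2.0 kg. This shows that bias is possible, not that it is likely here.
- *That the test is invalid through non-sphericity.* In simulations at n = 8 the uncorrected error rate ran from 5.0% to 11.8% by covariance structure, and Greenhouse-Geisser brought it to 2.4% to 5.2%. The protocol does not exclude such a correction.

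**Conclusion.** The point holds as a limited criticism of a named method. Repeated measures ANOVA uses complete cases only, in samples of about eight. At 2% to 10% missing per record it would keep roughly 7.2 down to 4.7 patients and 7.5 down to 5.8 therapists, and would discard about 8% to 34% of the patient records collected. These figures rest on assumed, independent missing rates. Staff workload makes some missed forms plausible, but the protocol supplies no rate. Bias follows only if missingness is related to progress, and the documents do not say that it will be.

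Separately, the omnibus F does not address the 2 kg benchmark, and the step that does carries no stated measure of uncertainty. The change is worth making but is not critical to the study.

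**What to change.** In both analysis sections, replace repeated measures ANOVA with a linear mixed model (SPSS MIXED, REML, small-sample degrees of freedom) with time as a categorical factor and every available record included. Keep the covariance simple enough for eight subjects, for example a random intercept or AR(1) residuals. A random intercept-and-slope model may not be stable at this size, and neither it nor the simpler models were simulated here.

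Name the estimates to report:

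- mean weight gain, session 4 minus baseline, with its 95% CI set against 2 kg
- post-session-4 minus baseline, with its 95% CI, for each therapist scale

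Binge/purge frequency should likewise use all available records. State the number of subjects and records behind each estimate.

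A random intercept assumes equal covariance between all time points, so its interval for session 4 can be too narrow if weights fan out. The paired mean gain with a t interval, in patients who have both weights, is a simple check. The mixed model is valid when missingness depends on recorded values. It does not repair missingness that depends on unrecorded ones.

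No rule scoring a missing session-4 weight as failure is needed. The plan states no responder count, and such a rule would treat an unsubmitted form as a poor outcome.

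The cost is wording, slightly more analysis work, and a need to simplify the model if it does not converge. Data and software are unchanged, and the Trial status section reports that no data cleaning or analysis has begun.

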### Research questions

Does our adaptation to vFBT maintain the key components of standard FBT by therapist self-report?Does our implementation approach for vFBT lead to implementation success at the participating sites, as measured by expert rating of fidelity to the vFBT model?What is the experience of implementation teams and patients/families implementing vFBT (and for therapists, does the experience change over time)?Do patients in vFBT demonstrate clinical outcomes similar to patients receiving standard FBT?

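### Question 4 asks whether virtual FBT gives outcomes similar to standard FBT, but its only comparator, a prognostic 2 kg early-gain threshold, cannot support that conclusion

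*Protocol article*

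**What the plan says.** Research questions, fourth question: "Do patients in vFBT demonstrate clinical outcomes similar to patients receiving standard FBT".

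Measures, Patient outcomes (question 4), introduces the 2 kg figure: "Weight gain of at least 2 kg following the first four sessions of FBT is highly predictive of final treatment outcome". The same paragraph then gives it a second role: "This will be our benchmark for comparing vFBT effectiveness to standard FBT".

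Analysis, Patient outcomes (question 4), names one test for weight: "Changes in weight and average number of binge/purge episodes per week over time will be analyzed using repeated measures ANOVA (using SPSS software". A separate sentence covers the comparison: "Weight gain will be compared against the benchmark of 2 kg gain after four sessions in standard FBT". It does not say whether the mean gain or the share of patients is set against 2 kg, or how the result is to be judged.

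Study design describes a pre/post multi-site case study and no standard-FBT arm. Sample size plans one family per therapist, eight in all. It reports that no sample size calculation was done and calls the number suitable for a feasibility study.

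**The concern.** The 2 kg figure changes meaning between its introduction and its use. It enters as a prognostic threshold, which is naturally read per patient: those who gain at least that much early tend to do well in the end. It is then used as if it were the result that standard FBT produces. A threshold that separates likely good from likely poor outcomes among FBT patients implies that some of them fall below it. It says nothing about their average gain or about how many reach it.

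Question 4 is the only one of the four questions about patient outcomes. If 2 kg stands in for the standard-FBT result, the report could call vFBT similar to standard FBT, or worse, when the study holds no information on how standard-FBT patients are distributed around 2 kg.

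**Working it through.** **1. What Question 4 needs and what the article supplies.**

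| Needed to conclude similarity | In the article |
|---|---|
| Outcome under standard FBT (mean gain or share reaching 2 kg) | Neither is given |
| A concurrent standard-FBT group | None described |
| A margin for similar | None |
| An analysis comparing vFBT with standard FBT | A comparison with 2 kg, its form unstated; the ANOVA concerns change over time within vFBT patients and does not involve 2 kg |

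**2. Mean and proportion are different questions.** If four-session gain has a symmetric distribution with a mean of exactly 2 kg, 50% of patients reach 2 kg. A group that meets the benchmark on the mean then has half its patients short of the threshold. Without the standard-FBT share, nobody can say whether 50% is good, usual or poor.

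**3. The stated sample size.** Four programs × two therapists × one family = 8, which matches the article. It is a recruitment count, so there is no power figure to reproduce.

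**4. Precision with n = 8.** The article gives no SD for four-session gain, so 1.0, 1.5 and 2.0 kg are assumed.

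- Half-width of the 95% CI for mean gain = t(0.975; 7) × SD / √8 = 2.365 × SD / 2.828. This gives 0.84, 1.25 and 1.67 kg, or 42% to 84% of the 2 kg benchmark (0.84/2 and 1.67/2).
- Exact (Clopper-Pearson) 95% CI for the share reaching 2 kg: 4/8 gives 16% to 84%; 6/8 gives 35% to 97%.

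**5. How much the answer would depend on an unstated rule.** Neither rule below is in the article; both are illustrations. The first uses a two-sided 5% one-sample t-test and the noncentral t distribution with 7 degrees of freedom and noncentrality (true mean − 2)/(SD/√8). The second uses the normal distribution of the sample mean, with standard error SD/√8.

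| Illustrative rule | True mean gain | Probability of passing at SD 1.0 / 1.5 / 2.0 kg |
|---|---|---|
| Not significantly different from 2 kg | 1 kg | 32% / 63% / 77% |
| Observed mean at least 2 kg | 1 kg | 0.2% / 3% / 8% |
| Observed mean at least 2 kg | 2 kg | 50% / 50% / 50% |

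The same data could lead to opposite statements depending on which rule is adopted. Neither rule compares vFBT with standard FBT.

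**The case against.** The best defence is context. This is an implementation case study that describes itself as a feasibility and pilot study. Weight is the subject of the last of four questions, and the other three do not depend on it. The analysis section calls the benchmark comparison a measure of clinical implementation success. The Discussion leaves the formal comparison to later work: "this research will help to inform further studies on how the virtual delivery of FBT compares with in-person". Whether to report a mean or a proportion, and with which interval, is detail that a condensed article may leave to a fuller document. The sources cited for the 2 kg figure may also contain a standard-FBT response rate, which cannot be checked here.

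Much of this stands. Eight families is not an error in a feasibility study, and the missing form of the comparison is not the complaint. Context does not repair the mismatch in the article's own words: the question asks for similarity, the measures section speaks of comparing effectiveness, and the figure offered for both is a predictor of outcome. A later analysis plan could add detail, but it could not make that threshold a standard-FBT result.

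A reader might go further and infer that eight patients would let a poor result pass as similar. The article does not support that. It states no rule that a non-significant difference from 2 kg counts as similarity, so the 32% to 77% above is conditional on a rule it does not contain. Under the observed-mean rule a true mean of 1 kg would seldom pass. Nor does the article offer the ANOVA p-value as evidence of similarity; the ANOVA and the benchmark comparison are in separate sentences.

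**Conclusion.** The point holds as a mismatch between question and comparator. As written, the analysis can describe weight change in vFBT patients and how it sits relative to a prognostic threshold. It cannot support a conclusion that outcomes are similar to standard FBT, or any comparative-effectiveness statement. That follows from the text alone and needs no assumption.

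The low precision adds to this. The interval for 4 of 8 rests only on n = 8; the half-widths for mean gain also rest on the assumed SDs and on roughly normal gains.

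This should be corrected because it changes what the study may conclude. It does not undermine the study as a whole.

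**What to change.** - **Question 4:** ask what proportion of vFBT patients reach the early-gain threshold of at least 2 kg after four sessions.
- **Measures and Analysis, Patient outcomes (question 4):** describe 2 kg as an early-response threshold throughout, and remove the wording that presents it as the gain in standard FBT or as a means of comparing effectiveness.
- **Analysis:** define the endpoint per patient (gained at least 2 kg, yes or no). Report the proportion with an exact 95% CI and the mean gain with a 95% CI, both descriptively.
- **Interpretation:** state that similarity to standard FBT will not be concluded. If the cited sources give a standard-FBT proportion reaching 2 kg, quote it beside the interval for context.

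This needs no extra patients or data, and the article reports that no data cleaning or analysis had begun. The cost is a few lines of rewording and a more modest clinical claim, in keeping with the Discussion's own aim of informing later comparative studies.
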